**b. Contact with healthcare system**

In this section, visits to the ER, clinic appointments and readmissions to the

645 hosp  
646 ital  
are  
reco  
rded.

| Contact with the healthcare system |                        |                   |                     |                           |                                           |                                                |
|------------------------------------|------------------------|-------------------|---------------------|---------------------------|-------------------------------------------|------------------------------------------------|
| Visit Type                         | Reason of visit        | Planned/Unplanned | Days Post Discharge | Results                   | Adverse Event                             | ADE                                            |
| Clinic                             | palliative care doctor | Planned           | 18                  | to talk about end of life | Adverse Event
 | Adverse Drug Event
 |
| ER                                 | pneumonia              | Unplanned         | 29                  | stayed in ER for 2 days.  | Adverse Event
 | Adverse Drug Event
 |

\*Note that if an event

657 occurred more than 30 days post-discharge this will be indicated.

658

| Conditions                                                 |                                 |                                                    |                     |                       |               |     |
|------------------------------------------------------------|---------------------------------|----------------------------------------------------|---------------------|-----------------------|---------------|-----|
| Condition                                                  | New/Worse Condition (Interview) | Details                                            | Days Post Discharge | How long did it last? | Adverse Event | ADE |
| The following events occurred after 30 days post-discharge |                                 |                                                    |                     |                       |               |     |
| pain in legs                                               | New                             | pt has been complaining that his legs are in pain, | 33                  |                       |               |     |

c. **Medication history**

- The **Admission** column on the left shows the medication and dosage the patient was taking prior to admission.
- The **Discharge** column shows what action (continued, modified, stopped) was taken with these medications at the time of discharge from the hospital (from med reconciliation).
- The **Interview** column contains changes in meds between discharge and the time of the interview, including medications stopped, restarted, or newly started post-discharge.

- If a medication was continued, it will remain **green** in each column (*see clopidogrel*).
- If a medication was modified at discharge from the hospital, the medication will be **orange** in the **Discharge** column. *Note that for a medication change at discharge, you will need to read the new dosage to see if it is an increase or decrease. The field that was modified will be indicated in bold.* If the medication in the interview column is green, this means it was continued at the modified discharge dose (*see nitroglycerin*).
- If the medication was modified following discharge, the medication will be **orange** in the **Interview** column. The arrow will indicate if this is an increase or decrease from discharge (*see ciclesonide*).
- If a medication is stopped at discharge, it will no longer appear in that column (*see pantoprazole*).
- If a medication was stopped post-discharge, this will be indicated in **red** (*see tamsulosin*).
- For changes recorded by the interviewer, by who, when and why the change was made will be indicated if applicable.
- Medications started at discharge from the hospital that were not taken prior to admission will not appear in the Admission column (*see acetaminophen*).
- medications that were started after the discharge from hospital will appear in **yellow**. If available, the information regarding why and when it was prescribed will be indicated (*see finasteride*). If no reason for starting could be elucidated from the interview it will say “none”
- Reminder: If a short-form interview was completed by the RA for a 30-day readmission, the medications in the Interview column represent the actions taken by the team at the time of readmission.

| Admission                                                             |   | Discharge                                                             |   | Interview                                                                                                                                                                                                                                 | ADE                      |
|-----------------------------------------------------------------------|---|-----------------------------------------------------------------------|---|-------------------------------------------------------------------------------------------------------------------------------------------------------------------------------------------------------------------------------------------|--------------------------|
| 
CLOPIDOGREL
 
75MG
TABLET
die
             | ➡ | 
CLOPIDOGREL
 
75MG
TABLET
die
             | ➡ | 
CLOPIDOGREL
 

                                                                                                                                                                                                        |  |
| 
FUROSEMIDE
 
40MG
TABLET
bid
              | ↕ | 
FUROSEMIDE
 
40MG
TABLET
die
              | ➡ | 
FUROSEMIDE
 

                                                                                                                                                                                                         |  |
| 
PANTOPRAZOLE
 
40MG
ENTERIC TAB.
qAM
      | ✕ |                                                                       |   |                                                                                                                                                                                                                                           |  |
| 
TAMSULOSIN
 
0.4MG
LA-TABLET
die
          | ➡ | 
TAMSULOSIN
 
0.4MG
LA-TABLET
die
          | ✕ | 
TAMSULOSIN
 
 
This medication was Stopped by Physician because None None
 
It's related to the following condition or visit: Unplanned Hospital 11 days since discharge
 
                                  |  |
| 
NITROGLYCERIN
 
0.8MG/HR
PATCH
die
        | ↕ | 
NITROGLYCERIN
 
1mg/hr
PATCH
die
          | ➡ | 
NITROGLYCERIN
 

                                                                                                                                                                                                      |  |
| 
CICLESONIDE-INH
 
400mcg
METERED INH.
die
 | ↕ | 
CICLESONIDE-INH
 
200mcg
METERED INH.
die
 | ⬇ | 
CICLESONIDE-INH
 
 
This medication was Decreased by Physician because Experienced reactions/side effects None
 
It's related to the following condition or visit: Planned Clinic 13 days since discharge
 
 |  |
|                                                                       |   | 
ACETAMINOPHEN
 
650MG
8H-TABLET
qid
       | ➡ | 
ACETAMINOPHEN
 

                                                                                                                                                                                                      |  |
|                                                                       |   |                                                                       |   | 
FINASTERIDE
 
 
This medication was prescribed because None 5mg
 
It's related to the following condition or visit: Unplanned Hospital 11 days since discharge
 
                                            |  |

694  
695  
696  
697

698  
699

7. In the Analysis section, you will select whether you believe the patient had an

Analysis

Did this patient have an ADVERSE EVENT starting within 30 days of discharge?:

✓

Yes

No

700  
701  
702  
703  
704  
705

8. ANY **Adverse Event** (may or may not be drug-related) within 30 days of discharge.

If NO, then click “Complete this Adjudication”. You will be asked to confirm that you

Did this patient have an ADVERSE EVENT starting within 30 days of discharge?:

No

COMPLETE THIS ADJUDICATION

706  
707  
708  
709  
710  
711  
712  
713

have completed the adjudication. If not, then select Cancel.

If YES, **scroll up** and select the Adverse Event checkbox on the far-right side next to the appropriate condition(s) or visit(s) you believe is related to the event.

\*Note: Do not select any events beyond 30 days unless you believe they clearly started within the 30-day period.

Did this patient have an ADVERSE EVENT starting within 30 days of discharge?:

Yes

Please select all events you believe are related to the adverse event.

714  
715

| Visit Type | Reason of visit | Planned/Unplanned | Days Post Discharge | Results                                   | Adverse Event                         |
|------------|-----------------|-------------------|---------------------|-------------------------------------------|---------------------------------------|
| ER         | 1st fall        | Unplanned         | 11                  | overnight stay in ER only, no readmission | 
Adverse Event
 
✓
 |

9. Next, select whether you think the patient's event was an **adverse DRUG event**. Select an option from 1 to 6. An **ADE is adjudicated as positive if 5 or 6 is selected**.

If option 1 to 4 is selected (not due to an adverse drug event), complete the adjudication. If option 5 or 6 is selected, **scroll up** and check off the ADE checkbox next to any and all condition(s), visit(s), and medication(s) you think are responsible.

Was there an ADVERSE DRUG EVENT?:

✓

- 1: outcome definitely caused by the patient's disease
- 2: outcome probably caused by the patient's disease
- 3: outcome more than likely caused by the patient's disease
- 4: outcome more than likely caused by the patient's medication
- 5: outcome probably caused by the patient's medication
- 6: outcome definitely caused by the patient's medication

10. Select whether or not you think at least one of the events was preventable (ex. a patient is newly started on quetiapine at discharge and returns to the ED a few days later with delirium; this could have been prevented if quetiapine had not been started.)

11. Select whether at least one event was ameliorable. (Ex. a patient has gastrointestinal hemorrhage and they are taking aspirin and coumadin. There is no obvious indication for taking both on an ongoing basis from examining the past medical history. Both drugs were continued at discharge. Aspirin could have been stopped.)

12. Select whether the ADE was related to a withdrawal event (e.g. secondary to reducing, tapering, or stopping a medication)?

Was at least one event preventable?:

✓

- Yes
- No
- Unable to determine

Was at least one event ameliorable?:

Was this ADE related to a withdrawal event (e.g. secondary to reducing, tapering or stopping a medication)?:

13. In some cases, the ADE is completely unrelated to the hospitalization. You should next select if the ADE is related to the hospitalization or not. Most ADEs are tied back to the hospitalization in some manner of speaking, but occasionally they are totally unrelated. Here is a real-life example: A patient visits their family doctor 10 days after hospital discharge and is newly prescribed gabapentin for leg cramps. At the time of the interview they state they have had new swelling in their legs since starting gabapentin and went to the ER for that. This is an adverse drug event. It is an ADE that is completely unrelated to the hospitalization, however. Here is another example: The

patient develops a rash on their leg and is given cefadroxil by their cardiologist at 20 days post discharge. They then develop anaphylaxis and must go to the ER. This is an adverse drug event. But it is completely unrelated to the hospitalization.

Once you have answered all the questions and selected all the appropriate checkboxes, click on the “Complete this Adjudication” button at the bottom of the page.

[figure not shown]

#### Examples of AEs

1. A patient is readmitted to the hospital at 26 days post hospital discharge with shortness of breath and cough. This patient had an adverse event. On the Likert scale for ADE, this was judged to be more than likely related to the patient’s medical conditions as opposed to one of their medications. Therefore, it is adjudicated as an adverse event, but not an ADE.
2. A patient takes aspirin chronically. The prescription remains unchanged at discharge from hospital. At 29 days post hospital discharge the patient presents to the ER with blood per rectum and they are told it is not serious and sent home. This is an adverse event (presents to the ER within 30 days post discharge). This was adjudicated as a 4/6 on the Likert scale (more than likely related to the medication). This is not certain enough to qualify as an ADE for this study. Therefore, the file is closed as an adverse event, but not as an ADE. We will do a planned secondary analysis that includes 4/6 adjudications. For the primary outcome of this study only 5/6 or 6/6 is classified as an ADE.
3. A patient with COPD is discharged and represents to the ER five days after discharge with dyspnea and in need of supplemental oxygen. This is an adverse event but not an adverse drug event (caused by underlying condition).
4. A patient develops shortness of breath, and pulmonary edema that requires a chest x-ray, Lasix, and nitro emergency treatment at their residence. Upon review of the medications, there were no changes at discharge that may have contributed. This adverse event was probably caused by the patient’s underlying condition.

## Examples of ADEs

1. A patient is prescribed **sertraline** newly at hospital discharge and begins to develop substantial **nausea and anorexia** in the 30-days post hospital discharge after starting sertraline. This is an adverse event and is ALSO AN ADE. It is probably related to the sertraline and was adjudicated as a 5/6 on the Likert scale. These are known side effects of the medication and started in a consistent timeframe.
2. A patient is taking chronic **pantoprazole**. At hospital discharge you see they are newly started on magnesium pills. One week after discharge the patient has a **traumatic fall** and in the ER, they tell her it is because she has **critically low magnesium levels**. She receives IV magnesium 3 times over the next month. All the while she has been on pantoprazole. This is an ADE. Hypomagnesemia is a recognized side effect of PPI therapy and can occur at any time (a paradoxical reaction) that the patient is taking the medication. This was adjudicated as a 5/6 on the Likert scale. There was no history of cancer or chemotherapy or other past medical condition to explain the low magnesium.
3. A patient is diagnosed with giant cell arteritis and started on **prednisone 50 mg po daily** and returns with upper GI bleeding the week following their discharge with **an ulcer** that requires cauterizing on gastroscopy. This is ADE secondary to prednisone. This is a known side effect of the medication.
4. A patient is **newly started on trazodone** for sleep at hospital discharge and returns to the hospital 1-2 weeks later with a **fall and bleeding in the head**. Sedation and falls are known side effects of medications with sedating properties prescribed for sleep. This was scored as 5/6 on the Likert scale.
5. At discharge from the hospital a patient is **started on asa** in addition to their usual clopidogrel. They are also **started on codeine 60 mg po QID**. Following this the patient develops **nausea and recurrent vomiting** for several days. The patient's son researches on the internet and stops the codeine and the patient feels better/vomiting diminishes in frequency and severity. This is an adverse drug event.

## Examples that DO NOT qualify as an Adverse Event:

1. A patient is discharged, and they have a **TIA at 31 days post hospital discharge**.  
REASON: For the primary study outcome we are only looking at events that occur up to 30-days post discharge. We do not include events that start after 30 days. For this to qualify as an adverse event it would need to have started on day 30 or earlier.
2. A patient is admitted with the principal diagnosis of stroke. After discharge they have several **planned visits** with their doctors including their ophthalmologist who performs an intraocular injection for fluid build-up in the eye. This is not an adverse event.
3. A patient is discharged from the hospital following admission for pneumonia. 26 days after discharge they develop a **sore throat** and see their family doctor. This is not an adverse event.
4. A patient is discharged following an admission for bacteremia. They develop **diarrhea** 29 days after discharge which resolves one day later on its own. This was not considered an adverse event or an adverse drug event (once medications and conditions reviewed).

- 826 5. A patient is readmitted to the hospital **32 days** after hospital discharge after being found  
827 on the floor at home with a temperature of 29C and altered level of consciousness. This  
828 cannot be adjudicated as an adverse event as it took place more than 30 days after  
829 hospital discharge unless you believe it started before day 30. Please do not adjudicate  
830 anything that takes place beyond 30 days post discharge unless it clearly starts within 30  
831 days of discharge.  
832

833 **Examples that are NOT classified as an ADEs:**  
834

- 835 1. A patient takes aspirin for ischemic heart disease and is diagnosed with mouth/throat  
836 cancer. They start bleeding from their mouth cancer following hospital discharge and  
837 need to go the ED and receive a blood transfusion. This is an adverse event. It was  
838 scored as 4/6 on Likert scale (the outcome was more than likely caused by the  
839 patient's drug). In this study, this will NOT be classified as an ADE for the primary  
840 outcome. In this case, it is not clear how much the disease contributed to the bleeding  
841 as opposed to the medication. Certainly, the aspirin contributed to the bleeding. We  
842 will do a preplanned sensitivity analysis including 4/6 along with 5 and 6/6 scores.  
843 2. A patient sees his cardiologist and family doctor for planned visits at 15 days post-  
844 discharge. The cardiologist decreases the furosemide from 40 mg po daily to 20 mg  
845 po daily and arranges to see the patient again in follow-up. This is normal clinical  
846 titration of furosemide and is not an adverse drug event.  
847 3. A patient has their diabetes medications decreased at hospital discharge. When they  
848 see their physician in follow-up the medications are further adjusted and some of the  
849 stopped medications are restarted. This is not an adverse drug event.  
850  
851  
852

## Section 8 – Assessment of Safety

### *8.1 Specification of safety parameters*

During adverse drug event adjudication, adverse drug events due to withdrawal of a drug (stopping, tapering, holding, accidental failure to represcribe or deprescribing) are captured in the case report form. Any adverse drug event that is from deprescribing will be reported as a secondary outcome (adverse drug withdrawal events).

### *8.2 The methods and timing for assessing, recording, and analysing safety parameters.*

Throughout the study, a study email is routinely monitored for reporting of any adverse events. Each deprescribing report contains the study email and the deprescribing report prompts the recipient to contact the study team in the event of any perceived adverse event. We will also have monthly meetings with study teams to obtain feedback on the tool and solicit any perceived adverse events. Finally, we will capture adverse drug withdrawal events and evaluate them over the course of the study and associated with the intervention.

### *8.3 Procedures for eliciting reports of and for recording and reporting adverse event and intercurrent illnesses.*

All deprescribing reports contain the contact information for the principal investigator/study email and the treating team is encouraged to contact the study team in the event of an adverse event. Otherwise, adverse events are collected and analyzed at the end of the study and are captured in the case review file as adverse drug withdrawal events.

### *8.4 The type and duration of the follow-up of subjects after adverse events.*

Subjects who have an adverse event receive usual hospital care. Follow-up is limited to the 30-day telephone screening questionnaire. No long-term follow-up after an adverse event is planned other than usual care (presenting as needed to a usual treating physician, urgent care service, or emergency department).

## Section 9 – Statistics/Statistical Analysis Plan

### 9.1a *A description of the statistical methods to be employed, including timing of any planned interim analysis(es).*

Baseline characteristics will be expressed as numbers and percentages for categorical variables and median and interquartile range (IQR) for continuous variables. Differences between control and intervention baseline characteristics will be compared by chi-square or rank-sum as appropriate (for descriptive purposes since this is a cluster randomized trial and there may be chance imbalances due to case-mix during the intervention and control periods).

All analysis will be by intention to treat except where otherwise noted.

#### Primary Outcome - Adverse Drug Events

A mixed-effects logistic regression model will be used for the outcome of adverse drug events ( $\geq 5$  on Leape-Bates scale) which controls for intervention, time period, and number of baseline potentially inappropriate medications as fixed effects and cluster as a random effect. This model will be used to estimate adjusted risk differences.

A sensitivity analysis will be conducted (supplemental) using a Leape-Bates Scale of  $\geq 4$  for the definition of adverse drug events.

This analysis will be conducted on patients who have consented to, and participated in, the post-discharge follow-up.

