It is our belief that the overall quality of prescribing on the units involved will increase, and our hope is that trainees will continue to practice safe prescribing through repeated exposure to the rulesets. This is one of the major goals/benefits of our project and why we were particularly interested in working on medical clinical teaching units across Canada.

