## Section 4: Trial Design

*4.1 A specific statement of the primary endpoints and the secondary endpoints, if any, to be measured during the trial.*

*Primary outcome:* Any adverse drug event within 30-days of hospital discharge (as defined by a 5 or 6 on the Leape and Bates scale). ADEs could include adverse drug withdrawal events (ADWEs).

*Secondary outcomes:*

- Proportion of patients with one or more PIM discontinued at discharge
- Absolute number of medications at discharge
- Absolute number of PIMs at discharge
- Adverse drug withdrawal events within 30-days post discharge
- Absolute number of medications at 30 days post-discharge
  - Proportion of medications that remain deprescribed at 30 days post-discharge
- Adverse events within 30-days post discharge
  - 30-day readmissions (ER or hospitalization) within 30-days post discharge
  - 30-day mortality in those that survive to hospital discharge
  - Falls within 30-days of hospital discharge
- 30-day post-discharge sleep questionnaire responses
- 30-day self-reported health-related quality of life

*Sensitivity analyses:*

- Adverse drug events as defined by a 4,5 or 6 on the Leape and Bates scale

*Effect by:*

- Biological sex
- Admission from a long-term care home
- Palliative status
- Frailty status (dichotomized as moderate to severely frail vs not)

*4.2 A description of the type/design of trial to be conducted (e.g., double-blind, placebo-controlled, parallel design) and a schematic diagram of trial design, procedures, and stages.*

This is a cluster randomized trial comprising 3 clusters: Quebec, Ontario, and Western Canada (Alberta and British Columbia).

*4.3 A description of the measures taken to minimize/avoid bias, including:*

(a) Randomization

The order that the cluster enters intervention is randomized prior to the start of the study.

(b) Blinding and Allocation Concealment

Study sites will only learn that they are crossing over to the intervention 4 weeks prior.

Healthcare personnel and patients at participating sites will remain blinded to the specific objectives of the study while in the control phase. They will be aware that we are conducting a study of post-discharge adverse events; however, they will not know that we are specifically looking at medication appropriateness, deprescribing, and adverse drug events. When study sites cross into intervention it will no longer be possible to blind them to the objectives.

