*Sensitivity analyses as indicated above.*

*9.1b A description of the post-hoc statistical methods to address imbalances between the cluster and the intervention groups*

We performed 5 post-hoc sensitivity analyses to address the low number of clusters in the study: 1) an analysis adjusting for patient factors that differed between groups by  $P < 0.01$ ; 2) treating clusters as a fixed-effect; an analysis with 3) a random and 4) fixed effect for hospital ( $n=11$ , in lieu of cluster) and 5) using permutation, a non-parametric method of evaluating for the weighted within period effect size.

*9.2 The number of subjects planned to be enrolled (sample size calculation)*

The expected proportion of medical patients who will experience an ADE after discharge is between 10 and 19%. For our power calculation we have used the midpoint, 15%. Type

1 error will be 5% and type 2 will be 20%. The cluster correlation expected is no more than 0.03. We wish to show an absolute decrease of four percent. An 8400-patient trial comprising 6 clusters who each recruit 200 patients per cluster-period will have 80% power to detect a change in ADE of from 15% to 11.2% or lower (an absolute risk reduction of 3.8%, number needed to treat 27). Implementation of this power calculation used the Stata function “steppedwedge” and followed the Hussey and Hughes approach.

*Revised prior to the recruitment of the first 200 patients to any cluster to:*

Three clusters will be created based on geographical location in Canada (Quebec, Ontario, Western Canada). These clusters are expected to enroll 500 subjects per time period for a total of 1 baseline and 3 randomized time-periods. The total number of patients will be 6000. With an estimated 15% adverse drug event rate, this will yield at least 80% power to detect an absolute difference of 4.8% (NNT 21) with an alpha of 0.05 and varying intra-cluster correlation ranging from 0.01 to 0.05.

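### The single-term primary model in 9.1a weights exposure periods 1, 2 and 3 by about 1.2, 0.1 and -0.3, so it mainly estimates the early effect and misstates the average if the effect changes with exposure

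*Protocol*

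**What the plan says.** Section 9.1a of the protocol fixes the primary model for adverse drug events (ADEs). It is a mixed-effects logistic regression that "controls for intervention, time period, and number of baseline potentially inappropriate medications as fixed effects and cluster as a random effect", and adjusted risk differences are derived from it. No term depends on how long a cluster has been in the intervention.

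Section 4.2 gives the design: "This is a cluster randomized trial comprising 3 clusters: Quebec, Ontario, and Western Canada (Alberta and British Columbia"). Section 4.3 adds: "The order that the cluster enters intervention is randomized prior to the start of the study". The revised sample size in 9.2 reads "These clusters are expected to enroll 500 subjects per time period for a total of 1 baseline and 3 randomized time-periods", and "The total number of patients will be 6000".

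Section 2.5 states a belief that prescribing on the study units will improve, and continues: "our hope is that trainees will continue to practice safe prescribing through repeated exposure to the rulesets". It counts this among the project's major goals.

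Section 9.1b lists five post-hoc sensitivity analyses, written in the past tense. They are adjustment for imbalanced patient factors, cluster as a fixed effect, hospital as a random effect, hospital as a fixed effect, and a permutation analysis of a weighted within-period effect. None of them models time since crossover.

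**The concern.** In a stepped wedge, a single intervention term gives a fair average only if the effect does not depend on exposure time. Here every cluster is on intervention in the last period. The model therefore treats the last-period difference between the first and last clusters to cross as a standing cluster difference, and removes part of it from the estimate. If the first cluster looks better at that point because it has been exposed longest, some of its benefit is subtracted.

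Section 2.5 gives a concrete reason why the effect could change, since trainees may learn from repeated reports. If it does, the headline risk difference is not the average effect over the exposed periods. It is too small when benefit builds up and too large when benefit fades. A weak primary result could then mean either little benefit or a growing one.

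**Working it through.** **Inputs.** Three clusters (4.2); four periods and 500 patients per cluster-period, 3 × 4 × 500 = 6000 (9.2); control ADE rate 15%, ICC 0.01 to 0.05 and a 4.8-point difference (9.2); alpha 0.05 (9.3). Assumed: one cluster crosses per step (the diagram is not shown), equal cells, a two-sided test, and the Hussey-Hughes model for the revised calculation (9.2 names it for the six-cluster one).

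**The plan's own figure.** Generalised least squares on the 12 cluster-period means, with total variance 0.15 × 0.85 and ICC 0.03, gives a standard error (SE) of 1.715 points for the single-term effect. Power = Φ(4.8/1.715 − 1.96) = Φ(0.84) = 80%. With a variance averaged over the two arms, power is about 84 to 85%. The stated power of at least 80% is reproduced under a constant effect.

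**Weights.** Coefficients of the single-term estimate on the cell means at ICC 0.03:

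| Cluster | Period 1 | Period 2 | Period 3 | Period 4 |
|---|---|---|---|---|
| First to cross | -0.292 | 0.500 | 0.104 | -0.292 |
| Second | 0.000 | -0.396 | 0.396 | 0.000 |
| Third | 0.292 | -0.104 | -0.500 | 0.292 |

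Summing the treated cells by exposure period:
- Exposure 1: 0.500 + 0.396 + 0.292 ≈ 1.19
- Exposure 2: 0.104 + 0.000 ≈ 0.10
- Exposure 3: -0.292 ≈ -0.29

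The weights sum to 1. They are 1.167/0.111/-0.278 at ICC 0.01, 1.193/0.102/-0.296 at ICC 0.05, and 1.20/0.10/-0.30 with fixed cluster effects.

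**Consequences.** Estimate = 1.189 d1 + 0.104 d2 − 0.292 d3, where d is the change in ADE risk in points (negative is benefit). The within-period column uses period 2 (exposure 1 only) and period 3 (exposures 1 and 2 equally). Periods 1 and 4 have no contrast. With equal period weights (assumed), that is 0.75 d1 + 0.25 d2.

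| Assumed d1/d2/d3 | Equal average | Average over treated cells (3:2:1) | Primary model | Within-period |
|---|---|---|---|---|
| -4.8/-4.8/-4.8 | -4.8 | -4.8 | -4.8 | -4.8 |
| -3.6/-4.8/-6 | -4.8 | -4.4 | -3.0 | -3.9 |
| -2/-4/-6 | -4.0 | -3.3 | -1.0 | -2.5 |
| -1/-3/-5 | -3.0 | -2.3 | 0.0 | -1.5 |
| 0/-4.8/-4.8 | -3.2 | -2.4 | +0.9 | -1.2 |
| -6/-4/-2 | -4.0 | -4.7 | -7.0 | -5.5 |

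Under linear growth d2 = (d1 + d3)/2, so the estimate is 1.241 d1 − 0.240 d3. It reaches zero only when d3 is about 5.2 times d1.

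For the mild case, power is Φ(3.02/1.715 − 1.96) ≈ 42%, or 46 to 48% with the averaged variance.

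**Scale check.** The weights are exact for the linear model. A binomial logit model with fixed period and cluster effects, fitted to expected counts, gives adjusted risk differences of -2.93 for -3.6/-4.8/-6, -0.92 for -2/-4/-6 and +1.03 for 0/-4.8/-4.8. The pattern is the same.

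**Cost of exposure terms.** Replacing the single term with three exposure indicators and averaging them gives an SE of 2.61 to 2.67 points, against 1.70 to 1.72. Power for a 4.8-point average at ICC 0.03 is then Φ(4.8/2.67 − 1.96) ≈ 44% (47 to 50% with averaged variances).

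**The case against.** Section 2.5 voices a belief and a hope about prescribing. It does not say that the ADE effect will grow from period to period. The described mechanism can act at once: an individual report during the admission, judged on that admission's discharge prescription and on 30-day events. A constant effect is compatible with this, and the model then recovers it. This stands. A reader might infer that the protocol expects a growing effect and so contradicts its own model, but the text supports only that growth is plausible.

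A reader might also infer that nothing in the plan could reveal the problem. That is too strong. The within-period analysis in 9.1b has no negative weights and would diverge from the primary in the growth scenarios above. It is a partial safeguard, because period 4 has no control cluster and the third exposure gets zero weight.

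The size depends on the pattern and the comparator. Mild growth attenuates without changing sign, and the third exposure is only one of six treated cells. The protocol does not name an equal-exposure average as its target, but the growth estimates also fall short of the average over treated cells. Negative weights are not peculiar to three clusters either; the superseded six-cluster design had them at its three longest exposures, though smaller (-0.03 to -0.12 each).

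Finally, extra supportive models are often left to a separate analysis plan. But the primary model is fixed here, and section 9 itself lists the sensitivity analyses.

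**Conclusion.** The point holds in a conditional form. With three clusters and four periods, the primary estimate is essentially the first-exposure effect, with weights of about 1.2, 0.1 and -0.3 across the protocol's ICC range. It equals the average effect only if the effect is constant. Plausible growth attenuates it (-4.8 on average read as about -3.0; -4.0 read as about -1.0). Fading overstates it (-4.0 read as about -7.0). Zero or reversed estimates need steep or delayed growth.

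The documents do not support saying that the trial will give the wrong answer, or that its power figure is wrong; that figure is reproduced under the stated assumption. The conclusion rests on one crossover per step, equal cells of 500, an exchangeable ICC of 0.01 to 0.05, and the linear model as a close guide to the logistic one. The effect patterns are illustrations, not forecasts. The change should be made, since it is cheap and the headline result is hard to interpret without it.

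**What to change.** Keep the primary model. Add one supportive analysis that replaces the single intervention term with indicators for exposure periods 1, 2 and 3. Report the three risk differences and their average with 95% confidence intervals, beside the within-period estimate already listed in 9.1b. Section 9.1b describes its analyses as post hoc and done, so label the new one post hoc if analysis has begun.

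State in 9.1a that the primary estimate is an average effect only if the effect is constant over exposure, and otherwise mainly reflects early exposure. Do not make interpretation depend on the estimates agreeing in direction. The averaged estimate is too imprecise for that, and signs could differ by chance.

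The cost is one more model on data already collected. The averaged estimate has an SE of about 2.7 points against 1.7, and well under 80% power for 4.8 points, so it can only be supportive.
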